## 5 Harmonization of Olink and SOMAscan

### 5.1 Standardization of Shared Proteins

For proteins measured on both Olink and SOMAscan, we applied a  $\log_2$  transformation with a small offset. Two mapping methods were used: (i) an affine transformation aligning medians and scaling by the ratio of robust standard deviations (median absolute deviations), and (ii) quantile mapping, interpolating Olink distributions to match SOMAscan quantiles.

## 5.2 Imputation of non-overlapping proteins

Missing proteins in UKBB were imputed using elastic-net regression trained on SOMAscan data. Overlapping proteins served as predictors and non-overlapping proteins as targets. Models were internally cross-validated, with predictors and outcomes standardized prior to fitting. The trained models were then applied to mapped Olink data to generate imputed values on the  $\log_2$  scale, which were back-transformed to the linear scale. Imputed values were clipped to the 0.5th–99.5th percentile range of the SOMAscan distribution to avoid implausible extremes.

## 5.3 Robustness checks

Nonparametric bootstrapping with repeated resampling of the SOMAscan cohort was used to quantify uncertainty in imputation. Distributional similarity between mapped Olink and SOMAscan values was assessed using Kolmogorov–Smirnov tests, histograms, and quantile–quantile plots. The Kolmogorov–Smirnov tests showed all the P value > 0.9. Histograms and quantile–quantile plots for four representative proteins are shown below as examples.

[figure not shown]

[figure not shown]

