### **3.4 UK Biobank (Validation Cohort)**

The UK Biobank (UKB) is a large cohort of ~500,000 U.K. adults (ages 40–69 at enrollment, 2006–2010). We will validate APRS among UKB participants of African ancestry. Plasma proteomics were measured by the Olink platform in ~50,000 participants. Of these, 1,171 were of African descent, including 204 APOL1 high-risk individuals. Olink measurements will be log2-transformed and normalized; missing proteins (compared to SomaScan) will be imputed via multi-output penalized regression trained on PMBB data. Outcomes (eGFR, dialysis/transplant, mortality) are ascertained via linked clinical and registry data. Analyses are conducted under UKB Resource Application #273810.

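### SAP 5.3 measures imputation uncertainty in UK Biobank by resampling the SomaScan cohort; as it naturally reads, this captures model-fitting variability only, so held-out accuracy for each imputed APRS protein should replace it.

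*Combined protocol and SAP*

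**What the plan says.** Protocol 3.4 says that proteins absent from the Olink panel "will be imputed via multi-output penalized regression trained on PMBB data". SAP 5.2 gives the method: "Missing proteins in UKBB were imputed using elastic-net regression trained on SOMAscan data", with the overlapping proteins as predictors. It continues: "The trained models were then applied to mapped Olink data to generate imputed values". The values are back-transformed, and "Imputed values were clipped to the 0.5th–99.5th percentile range of the SOMAscan distribution to avoid implausible extremes". No residual term is added to the prediction.

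On accuracy, SAP 5.2 says only: "Models were internally cross-validated, with predictors and outcomes standardized prior to fitting". It reports no R2 or RMSE.

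SAP 5.3 then gives the one measure of imputation uncertainty: "Nonparametric bootstrapping with repeated resampling of the SOMAscan cohort was used to quantify uncertainty in imputation". It does not say which statistic each resample returned, how many resamples were drawn, or how the result enters the UK Biobank analysis. The section's other checks (Kolmogorov–Smirnov tests, histograms, Q–Q plots) compare the marginal distributions of mapped Olink and SomaScan values.

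**The concern.** The error in an imputed protein has three sources: the fitted model differs from the true regression; the protein varies around that regression; and a mapped Olink reading is not what SomaScan would have read on the same sample. Refitting on resampled SomaScan participants moves only the first. That component shrinks as the training cohort grows, even when the protein is essentially unpredictable, so a small spread is no evidence of good imputation.

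UK Biobank is one of two external validations and includes 204 APOL1 high-risk participants (Protocol 3.4). The APRS coefficients are fixed in PMBB training and carried over (SAP 6.4.3). A reader therefore needs to know how far the UK Biobank score is the nine-protein score and how far it is a surrogate built from other proteins. A tight bootstrap spread would reassure on that question without answering it.

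**Working it through.** **1. No figure to reproduce.** The documents give no interval, bootstrap SD, imputation R2, number of overlapping predictors or number of imputed APRS proteins. They also do not say which PMBB set trained the imputation models. Candidates are 680 (training set, Supplementary Table 1), 851 (derivation set, SAP 3) and 1,113 (Protocol 3.2). Everything below is illustrative.

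**2. What the bootstrap can see.** Let Y be the SomaScan value, X the overlapping proteins as SomaScan would read them, X* the mapped Olink values, m the true regression and m̂ the fitted one. Then

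Y − m̂(X*) = [Y − m(X)] + [m(X) − m̂(X)] + [m̂(X) − m̂(X*)].

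The spread of refitted predictions reflects the sampling variability in the second bracket. The first is missing unless held-out residuals are used. The third is missing whatever statistic is computed, because no participants measured on both platforms are described.

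**3. Least-squares approximation.** Coefficient variance averages σ²p/n and total prediction variance is σ²(1 + p/n), so

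total SD / coefficient-only SD = √(1 + n/p).

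Example, n = 851 and p = 50 effective predictors: √(1 + 17.02) = 4.24. A nominal 95% interval built from the coefficient-only SD then covers 2Φ(1.96/4.24) − 1 = 36%.

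| p (n = 851) | 10 | 25 | 50 | 100 | 200 | 400 |
|---|---|---|---|---|---|---|
| SD ratio | 9.28 | 5.92 | 4.24 | 3.08 | 2.29 | 1.77 |
| Coverage | 17% | 26% | 36% | 47% | 61% | 73% |

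**4. Elastic-net simulation.** Assumptions: L1 ratio 0.5, penalty chosen by 5-fold cross-validation and held fixed, 40 resamples of the training cohort, 204 new participants, no mapping error, one run per row. Units are SDs of the protein.

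| n | Predictors (non-zero) | True R2 | Held-out R2 | Bootstrap SD | RMSE | Ratio | Coverage of nominal 95% |
|---|---|---|---|---|---|---|---|
| 851 | 500 (10) | 0.30 | 0.28 | 0.144 | 0.873 | 6.04 | 24.5% |
| 851 | 500 (10) | 0.70 | 0.70 | 0.119 | 0.555 | 4.67 | 24.5% |
| 851 | 500 (100) | 0.30 | 0.14 | 0.221 | 0.953 | 4.31 | 31.4% |
| 851 | 500 (100) | 0.70 | 0.60 | 0.247 | 0.622 | 2.52 | 49.0% |
| 851 | 1,500 (10) | 0.30 | 0.22 | 0.162 | 0.900 | 5.55 | 23.5% |
| 851 | 1,500 (10) | 0.70 | 0.70 | 0.130 | 0.586 | 4.50 | 25.5% |
| 851 | 1,500 (150) | 0.50 | 0.27 | 0.232 | 0.859 | 3.70 | 39.7% |
| 851 | 1,500 (150) | 0.80 | 0.61 | 0.293 | 0.602 | 2.05 | 61.8% |
| 851 | 1,500 (150) | 0.95 | 0.88 | 0.215 | 0.321 | 1.49 | 69.1% |
| 1,113 | 1,500 (50) | 0.50 | 0.39 | 0.169 | 0.816 | 4.83 | 26.0% |

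The bootstrap SD was below the RMSE in every row, by a factor of 1.49 to 6.04. It also failed to rank proteins by quality: held-out R2 0.28 went with a spread of 0.144 (first row), while held-out R2 0.88 went with a wider spread of 0.215 (ninth row).

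**5. Do the distribution checks fill the gap?** No. They concern mapped shared proteins and marginal distributions. In a side check, quantile-mapping an unrelated gamma variable (1,171 values) onto a normal one (851 values) gave a Kolmogorov–Smirnov P of 1.0. Under quantile mapping, agreement of that kind follows from the mapping itself.

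**6. Would residual draws be a better main analysis?** Assumptions: 204 people, one imputed protein plus one clinical term, 20 draws, censoring at 10 years, assumed effect sizes. The C-index with the measured protein was about 0.73.

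| Imputation R2 | 0.2 | 0.4 | 0.6 | 0.8 |
|---|---|---|---|---|
| Deterministic imputation | 0.668 | 0.688 | 0.706 | 0.717 |
| With residual draws | 0.623 | 0.652 | 0.681 | 0.705 |

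Draws made without regard to outcome moved the C-index further from the measured-protein value at every R2.

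**The case against.** The strongest reply is that SAP 5.3 names the resampling unit but not the statistic. A bootstrap of the SomaScan cohort can return out-of-bag prediction error, which does include the residual, and SAP 5.2 already mentions cross-validation. This stands in part: the text does not prove that residual error was ignored. But neither out-of-bag nor cross-validated accuracy is reported, and neither could include cross-platform error.

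A reader might infer that the UK Biobank confidence intervals are several-fold too narrow. The documents do not support that. They report no such interval, and the factor above concerns one person's imputed protein. A C-index or time-dependent AUC for a score computed from deterministic imputed values is a different quantity, and poor imputation already lowers its point estimate, as step 6 shows.

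A reader might also infer that because elastic-net predictions have less spread than measured proteins, discrimination in UK Biobank is invalid. That does not follow either. Uniform compression leaves rank-based measures unchanged. Only a shift in the relative weight of imputed and measured components could change ranks, and its size is unknown while the number of imputed APRS proteins is unstated.

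Finally, this is a robustness check in one cohort. PMBB derivation and the ARIC validation, which uses SomaScan, do not depend on it.

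**Conclusion.** The point holds as a limited one about method and reporting. On its natural reading, the SAP 5.3 bootstrap measures model-fitting variability and not the error of the imputed proteins; on every reading it omits Olink-to-SomaScan mapping error. The direction follows from the decomposition in step 2 and needs no simulation.

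The size is assumption-dependent. For an individual imputed value, the bootstrap SD was about 1.5 to 6 times smaller than the actual error in the elastic-net runs, and only 1.5 to 2.5 times smaller for dense proteins with true R2 of 0.7 to 0.95. The least-squares approximation at n = 851 gave about 1.8 to 9. These rest on assumed predictor counts, sparsity, R2 and training size, with no mapping error. They say nothing about the width of any C-index or AUC interval. What is affected is how much a reader can conclude from the UK Biobank validation.

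**What to change.** 1. In SAP 5.3, replace the bootstrap spread as the measure of imputation uncertainty with out-of-fold R2 and RMSE for each APRS protein imputed in UK Biobank, taken from the cross-validation already run under SAP 5.2. List which of the nine proteins are imputed. If the bootstrap is kept, define its statistic and label it as model-fitting variability.

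2. In the PMBB test set, recompute APRS discrimination with those same proteins replaced by predictions from imputation models fitted without the test-set participants. Report the loss against the measured-protein score in the same people, with an interval for the difference. The test set has 171 participants and 32 composite events (Supplementary Table 1), so that interval will be wide.

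3. State that both results are a best case, because they are within SomaScan and exclude cross-platform mapping error.

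4. Keep any residual-draw multiple imputation as a labelled sensitivity analysis only, since draws that ignore outcome bias discrimination downward.

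The cost is a little computing and a wording change in the SAP. The downside is a possibly less favourable account of the UK Biobank validation.

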### Distributional Comparison Between Mapped Olink and SOMAscan Values for four Proteins

Histograms and quantile–quantile (Q–Q) plots compare the original SOMAscan (blue) and mapped Olink-to-SOMAscan (orange) measurements. Kolmogorov–Smirnov (KS) tests demonstrated no significant distributional differences.

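### The Kolmogorov–Smirnov result in SAP 5.3 is no evidence that Olink values stand in for SomaScan values in UK Biobank: after in-sample quantile mapping it passes by construction, and under either mapping it sees only marginal distributions.

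*Combined protocol and SAP*

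**What the plan says.** UK Biobank was assayed on Olink and the APRS is derived on SomaScan, so SAP 5 sets out how the platforms are bridged.

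- **Shared proteins (SAP 5.1).** Two mappings are listed: "an affine transformation aligning medians and scaling by the ratio of robust standard deviations (median absolute deviations"), and "quantile mapping, interpolating Olink distributions to match SOMAscan quantiles". Neither is named as primary. SAP 3 nevertheless calls the cross-platform mapping prespecified.
- **Proteins absent from Olink (SAP 5.2).** "Missing proteins in UKBB were imputed using elastic-net regression trained on SOMAscan data". "Overlapping proteins served as predictors and non-overlapping proteins as targets". The fitted models are then applied to the mapped Olink data, so imputed values inherit any error in the mapping. The models are said to be internally cross-validated.
- **Checks (SAP 5.3).** The SomaScan cohort is bootstrapped to express imputation uncertainty. Then: "Distributional similarity between mapped Olink and SOMAscan values was assessed using Kolmogorov–Smirnov tests, histograms, and quantile–quantile plots". The result is "The Kolmogorov–Smirnov tests showed all the P value > 0.9", and the figure legend concludes that "Kolmogorov–Smirnov (KS) tests demonstrated no significant distributional differences".

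No sample held out from fitting the map is described. No persons measured on both platforms, no person-level correlation and no accuracy figure for any imputed protein are reported. The documents do not say which of the nine APRS proteins are measured and which imputed in UK Biobank.

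**The concern.** Quantile mapping replaces each Olink value with the SomaScan value of the same rank. Asking afterwards, on the same data, whether the two distributions differ tests the interpolation and not the assay. The histograms and quantile–quantile plots share this weakness. A protein whose Olink reading carries no information about the SomaScan reading would pass as easily as a good one.

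UK Biobank is one of two external validations, with 204 APOL1 high-risk participants (Protocol 3.4). The APRS combines nine proteins with age, sex, eGFR and UACR (Protocol 3.7). If several proteins carry little signal after mapping and imputation, a weak UK Biobank result cannot be told from a score that does not transport. A good result could rest on the four clinical covariates. An overall C-index does not separate these cases, and the SAP's reported checks do not either.

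**Working it through.** The documents give no protein-level data, so the check simulates the procedure they describe.

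**Inputs.** Olink n = 204 or 1,171 (Protocol 3.4). SomaScan n = 851 (SAP 3), 1,113 (Protocol 3.2), or 1,113 + 995 = 2,108 (adding the low-risk set in SAP 3). Which subsets were used to fit the map is not stated, so these are assumptions. So are the five Olink shapes (normal, gamma, t with 3 df, exponential, bimodal). There were 300 runs per setting unless noted, with two-sided tests.

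**1. Why the quantile map passes.** Let m and n be the Olink and SomaScan sample sizes. After a full-rank in-sample map, the two empirical distribution functions can differ by no more than about 1/m + 1/n. The large-sample 5% critical distance is √(−ln(0.025)/2) × √((m+n)/(mn)).

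| m, n | 1/m + 1/n | 5% critical distance |
|---|---|---|
| 204, 851 | 0.0061 | 1.358 × 0.0780 = 0.106 |
| 1,171, 851 | 0.0020 | 1.358 × 0.0450 = 0.061 |

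The attainable distance is a small fraction of what the test needs in order to reject.

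**2. Reproducing the reported result.** With a full-rank or 101-point map, the minimum P was 1.0 for every shape and sample size. This matches the SAP's uniform P > 0.9.

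**3. Whether passing depends on agreement.** For 851 simulated persons measured on both platforms:

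| Between-platform correlation | Minimum P | Correlation of mapped with true value |
|---|---|---|
| −0.9 | 1.0 | −0.90 |
| 0 | 1.0 | 0.00 |
| 0.3 | 1.0 | 0.30 |
| 0.6 | 1.0 | 0.60 |
| 0.9 | 1.0 | 0.90 |

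The test gives the same answer throughout.

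**4. What P > 0.9 looks like without fitting.** Two unmapped samples from one distribution gave P > 0.9 in 9.4 to 9.6% of 4,000 runs. For four independent proteins that is about 0.096⁴ = 0.00008. When the quantile map was fitted on half of each sample and tested on the other half (gamma shape, 2,000 runs), P > 0.9 occurred in under 1% of runs and P < 0.05 in about 28%. So an out-of-sample version can fail.

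**5. The affine map.** With identical shapes, P > 0.9 occurred in about 25% of 4,000 runs (four independent proteins: about 0.25⁴ = 0.004). With gamma or exponential shapes it never occurred, and P < 0.05 occurred in 57 to 100% of runs.

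**6. A coarse quantile grid.** With 11 points, P fell below 0.9 in 8 to 100% of runs, depending on shape and sample size, and occasionally below 0.05. The test then measures interpolation error only.

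**7. Imputed values.** Linear predictions have less spread than the variable they predict. Simulated without clipping at R² of 0.1 to 0.5, they gave P < 0.05 in 75 to 100% of runs and never P > 0.9. Even at R² = 0.9, P > 0.9 occurred in only 4 to 7% of runs. This agrees with the text, which reports the test for mapped values and not for imputed ones.

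**The case against.** Four points can be made for the plan.

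- **The tested mapping is unknown.** This stands. That the test cannot fail, or that quantile mapping produced the P values, is something a reader might infer. The SAP does not say so, and the affine map and a coarse grid can both fail. Uniform P > 0.9 points towards a fine quantile map but does not prove it. If the affine map was tested, the result does say something about distributional shape, though still nothing about persons.
- **The SAP claims only distributional similarity.** This is fair. It does not present the test as proof of person-level agreement or imputation accuracy, and no decision rule depends on it. But the result appears under robustness checks for a bridge on which the UK Biobank validation relies, and equal marginals are not the property that matters there.
- **Imputation has its own checks.** Internal cross-validation and the bootstrap are real and should be credited. Both stay within SomaScan, and the SAP gives no accuracy figure from either. A masking exercise in PMBB is close to that cross-validation, so much of the request is to report it per protein and carry it through to discrimination. Such an exercise never touches Olink and cannot show that mapped values track SomaScan values.
- **The effect on discrimination may be small.** Forcing UK Biobank onto PMBB distributions removes real cohort differences, but a pure shift in a protein adds a constant to a linear score and leaves ranking within UK Biobank unchanged. Calibration and absolute-risk thresholds are more exposed. The same loss occurs with any mapping that lacks bridging samples, so it is not a fault of this test. ARIC used SomaScan and needs no Olink mapping.

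**Conclusion.** The concern holds in a conditional form. If the tested map was quantile, in-sample and on a fine grid, the reported P values carry no information: P is about 1.0 at any between-platform correlation tried, from −0.9 to 0.9. If the map was affine, uniform P > 0.9 would be unusual, and the test would still address only marginal distributions. In both cases it does not cover the imputed proteins.

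It would go too far to conclude that the mapping is wrong, that the imputation is poor or that the UK Biobank validation fails. The documents contain nothing that shows any of these. They show that the evidence offered cannot distinguish good from bad.

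The sizes rest on assumed shapes and sample sizes. The quantile-map result did not vary across those tried. The four-protein products also assume independent proteins and are only illustrative. The point should be addressed before the UK Biobank result is interpreted. It does not affect the derivation or the ARIC validation.

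**What to change.** 1. Stop citing the Kolmogorov–Smirnov result as evidence of robustness. Name one mapping as primary and report the other as a sensitivity analysis.
2. State which of the nine APRS proteins are measured and which are imputed in UK Biobank. In held-out PMBB samples, mask the imputed ones and predict them with the training-set model. Report R² and Spearman correlation for each protein, and the change in C-index and time-dependent AUC between the APRS with imputed and with measured proteins.
3. In UK Biobank, report a model with the four clinical covariates alone beside the APRS.
4. State as limitations that, without samples measured on both platforms, cross-platform agreement is untested, and that mapping UK Biobank onto PMBB distributions removes real cohort differences, mainly at the expense of calibration and absolute-risk thresholds.

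Items 1 to 3 use data in hand and take a few hours of analysis; item 4 is text. The price is that the reported imputation quality in UK Biobank may look less favourable than it does now.

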### Distributional Comparison Between Mapped Olink and SOMAscan Values for four Proteins

Histograms and quantile–quantile (Q–Q) plots compare the original SOMAscan (blue) and mapped Olink-to-SOMAscan (orange) measurements. Kolmogorov–Smirnov (KS) tests demonstrated no significant distributional differences.

## 6 Statistical methods

### 6.1 Missing Data Handling

Missing data is assumed to be missing at random. Missing data was handled across the entire PMBB dataset. Variables with >15% missingness were excluded. Remaining missing values were imputed using multiple imputation by chained equations; imputation was performed separately within the training and test sets to avoid information leakage. The UACR missing rates were 5.77% for APOL1-HR participants with eGFR > 60, 6.77% for APOL1-LR participants with eGFR > 60, and 2.80% for APOL1-HR participants with eGFR ≤ 60.

### 6.2 Statistical Analysis for Multiplicity Correction

We will address multiple hypothesis testing by applying Benjamini-Hochberg false discovery rate (FDR) correction to all univariate analyses of proteomic biomarkers, ensuring that the overall rate of false positives remains controlled. Specifically, we will first calculate raw p-values from Cox proportional hazards models (or comparable methods) for each protein, then adjust these p-values using FDR at a predefined threshold (e.g., FDR < 0.05). In cases where a more stringent control of type I error is required—such as validating a smaller panel of

high-priority protein biomarkers—we will consider Bonferroni or Holm-Bonferroni methods. All statistical analyses will be performed using Python (including the `statsmodels.stats.multitest` module) and R (e.g., the `p.adjust` function) to maintain reproducibility. Finally, we will report effect estimates (with 95% confidence intervals) for each protein and appropriately highlight any exploratory findings that do not undergo formal multiplicity adjustment.

### **6.3 Cox proportional hazards model**

#### **6.3.1 Censoring and the Assumption of Independence**

In survival data analysis, censoring occurs when an event is not observed due to termination of follow-up, loss to follow-up, or other reasons. To obtain unbiased estimates using Kaplan–Meier curves and Cox models, it is crucial that the censoring mechanism is independent of the actual event occurrence time. In this study, for outcomes other than death, patients censored due to loss to follow-up or the end of the 10-year follow-up period are assumed to be censored non-informatively.

Importantly, since all-cause mortality is included as an event within our composite outcome, deaths are treated as events rather than censoring. To address potential undercounting of events when using single-outcome definitions and to appropriately account for the competing risk of death, we construct a composite outcome that comprises  $\geq 40\%$  decline in eGFR, end-stage kidney disease, long-term dialysis, kidney transplantation, and all-cause mortality.

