## 2. Objectives

The primary and secondary objectives are to:

- Develop and validate a plasma APOL1 proteomic risk score (APRS) for prediction of a composite kidney outcome ( $\geq 40\%$  decline in eGFR, initiation of dialysis or kidney transplantation, or all-cause death) in APOL1 high-risk individuals with preserved kidney function.

- Compare APRS performance (discrimination) to standard models including the KFRE, APOL1 genotype status, and CKD polygenic risk scores.

- Externally validate APRS in independent, ancestry-matched cohorts (ARIC and UK Biobank) using harmonized outcomes.

- Assess biological plausibility by evaluating the association of APRS protein components with kidney tissue pathology (e.g., interstitial fibrosis).

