### **3.6 Study Endpoints and Follow-Up**

The primary endpoint is a composite defined as the earliest of: (1)  $\geq 40\%$  decline in eGFR from baseline; (2) onset of kidney failure (initiation of maintenance dialysis or kidney transplantation); or (3) all-cause mortality. These criteria mirror standard endpoints in CKD trials. Follow-up begins at the date of the index blood draw and continues until occurrence of the composite event, death, loss to follow-up, or end of study (up to ~10 years). Participants will be censored at the time of death if it precedes kidney endpoints, loss to follow-up, or at 10 years of follow-up to ensure comparability across cohorts.

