### **3.7 Statistical Analysis**

The APOL1–high-risk cohort will be randomly divided into an 80% training set and 20% test set (stratified by outcome incidence). In the training set, candidate proteins will be selected via an elastic-net penalized Cox proportional hazards regression (age, sex, baseline eGFR, and log2(UACR) included as unpenalized covariates). Tuning parameters ( $\alpha$ ,  $\lambda$ ) will be chosen by 8-fold cross-validation. The final APRS model will include the nine selected proteins plus the four clinical covariates. Model discrimination will be quantified

by time-dependent AUC (tAUC) at prespecified time points and Harrell's C-index. Model performance will be compared to the KFRE (4-variable equation) and established CKD risk scores.

Proportional hazards assumptions for APRS and covariates will be tested using Schoenfeld residuals. Sensitivity analyses will address potential biases: we will apply inverse-probability-of-censoring weighting (IPCW) to account for informative loss-to-follow-up, computing weights within the training set. Feature stability will be assessed via bootstrap resampling. We will compute net benefit using decision-curve analysis (assuming equal weight for false positives and negatives). To gauge clinical utility, we will calculate the number needed to treat (NNT) to prevent one composite event under a hypothetical APOL1-targeted therapy: assuming a relative risk reduction of 27% (as reported for inaxaplin), NNT will be derived as the reciprocal of the absolute risk reduction. Comparisons of NNT between APRS-based risk stratification and standard models (KFRE) will be reported. All tests will be two-sided with  $\alpha=0.05$ .

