## **1 Primary aim**

To develop and externally validate a proteomic-clinical risk score (APRS) that predicts incident, clinically meaningful kidney outcomes among APOL1 high-risk (APOL1-HR) adults with preserved baseline kidney function, thereby enabling earlier identification and targeting for upstream intervention.

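### APRS is meant to predict kidney outcomes, but its performance and NNT are specified only for a composite that includes death from any cause

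*Combined protocol and SAP*

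**What the plan says.** SAP section 1 wants a score that "predicts incident, clinically meaningful kidney outcomes among APOL1 high-risk (APOL1-HR) adults with preserved baseline kidney function". Protocol section 2 calls the endpoint a composite kidney outcome, but the definition ends with "initiation of dialysis or kidney transplantation, or all-cause death) in APOL1 high-risk individuals with preserved kidney function". Protocol 3.6 lists all-cause mortality as component (3).

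SAP 6.3.1 says that "deaths are treated as events rather than censoring", and gives this among its reasons: "to appropriately account for the competing risk of death, we construct a composite outcome". Protocol 3.6, after listing death as a component, also says: "Participants will be censored at the time of death if it precedes kidney endpoints".

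SAP section 7 defines time-dependent AUC and every other metric on one true/false event indicator, with no event type. Protocol 3.7 sets out the "number needed to treat (NNT) to prevent one composite event under a hypothetical APOL1-targeted therapy", using a 27% relative risk reduction (RRR). SAP 6.5 refers only to an event, without naming the type, and adds RRRs from 15% to 60%.

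Kidney events and deaths are counted separately in Supplementary Table 1 and in Appendices 1 to 3. Neither document specifies a cause-specific, subdistribution or cumulative-incidence analysis of APRS, a kidney-only discrimination measure, or a kidney-only NNT.

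**The concern.** The aim and the measured outcome differ. For the declared composite, treating death as an event is coherent: no one is censored by dying. But the outcome then becomes kidney event or death, and nothing in the plan says how well APRS ranks people by kidney risk, or what that risk is when death can come first.

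Three things depend on this. First, claims that APRS identifies carriers who will progress would rest on an outcome of which about a fifth is death without a kidney event. Second, a main comparator is a kidney-failure equation. A score trained on kidney-or-death and judged on kidney-or-death may gain part of its advantage from the death component, and no planned analysis would separate the two. Third, the NNT applies one RRR, for an APOL1-targeted drug, to every composite event, including deaths without a kidney event, and the documents give no basis for doing so.

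In addition, the two rules for death in Protocol 3.6 would let two analysts code the same participant in opposite ways.

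**Working it through.** **1. Reproducing the plan's figures.** Inputs: Appendix 1 (eGFR>60), 851 high-risk and 874 matched low-risk participants. Pearson chi-square without continuity correction returns the printed P values. Risk ratios (RR) have log-normal 95% intervals.

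| Outcome | High-risk | Matched low-risk | RR (95% CI) | P, recomputed | P, printed |
|---|---|---|---|---|---|
| Composite | 153 (17.98%) | 135 (15.45%) | 1.16 (0.94–1.44) | 0.16 | 0.16 |
| Death | 62 (7.29%) | 68 (7.78%) | 0.94 (0.67–1.30) | 0.70 | 0.7 |
| Kidney event | 120 (14.1%) | 86 (9.84%) | 1.43 (1.10–1.86) | 0.006 | <0.01 |

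The genotype contrast is weaker for the composite than for kidney events. No difference in death is detected.

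**2. Deaths without a kidney event** = composite − kidney events, taking the composite as the union of kidney events and death.
- High-risk: 153 − 120 = 33; 33/153 = 21.6% of composite events.
- Training set (Supplementary Table 1): 121 − 96 = 25; 25/121 = 20.7%.
- Test set: 32 − 24 = 8; 8/32 = 25%.
- Matched low-risk: 135 − 86 = 49. Comparing 33/851 (3.88%) with 49/874 (5.61%) gives P = 0.09.

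**3. Death by genotype elsewhere.**
- Appendix 2 (eGFR≤60, matched): 57/262 versus 2/38, RR 4.13 (1.05–16.24), P = 0.02.
- Appendix 3 (all, matched): 119/1113 versus 70/912, RR 1.39 (1.05–1.85), P = 0.02.
- Appendix 2 has only 38 matched low-risk participants. Appendix 3 remains unbalanced on eGFR after matching (78.26 versus 89.94, P<0.01).

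**4. Crude NNT** = 1/(RRR × event proportion), over the whole eGFR>60 high-risk cohort.

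| RRR | Composite (153/851) | Kidney only (120/851) |
|---|---|---|
| 15% | 37.1 | 47.3 |
| 27% | 1/(0.27 × 0.1798) = 20.6 | 1/(0.27 × 0.1410) = 26.3 |
| 60% | 9.3 | 11.8 |

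The ratio is 153/120 = 1.275 throughout. These are proportions over follow-up, not threshold-specific 5- or 10-year risks.

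**5. How far death alone could carry the composite AUC.** Ignoring censoring weights, the composite AUC is the case-weighted average of the AUCs for the two case types against the same event-free controls. A score with 0.5 for kidney events and 1.0 for death-only events gives 0.784 × 0.5 + 0.216 × 1.0 = 0.61 (0.75 × 0.5 + 0.25 × 1.0 = 0.625 with the test-set counts). A composite AUC of 0.80 needs at least (0.80 − 0.216)/0.784 = 0.745 for kidney events.

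Differences between scores decompose in the same way. As an illustration, an advantage of 0.10 confined to death-only cases would add 0.216 × 0.10 = 0.02 to the composite AUC with no gain for kidney events.

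**The case against.** The composite is declared openly and is a legitimate primary endpoint. It does remove informative censoring by death for that endpoint. Protocol 3.7 labels the NNT as hypothetical and per composite event, and the SAP's range of RRRs absorbs the gap: 27% × 120/153 = 21.2% on the composite gives the kidney-only NNT, and 21.2% lies within 15–60%. All of this stands. It is why the composite can stay and why the remedy is an added analysis.

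Four stronger readings are tempting, and the documents do not support them.
- A reader might infer that death is unrelated to APOL1 genotype. Only Appendix 1 points that way, and its interval (0.67–1.30) means no difference detected. Appendices 2 and 3 show more deaths in high-risk carriers, although in small or eGFR-unbalanced comparisons.
- A reader might infer that the composite masks the kidney signal. Dilutes is the right word: 120 of 153 high-risk composite events (78%) include a kidney event. An approximate rate ratio using N × mean time to event, 153/(851 × 6.51) against 135/(874 × 7.24), is 1.29 (1.03–1.63), which excludes 1; the same method gives 1.59 (1.21–2.10) for kidney events. This contrast is also between genotypes and says nothing direct about APRS within high-risk carriers.
- A reader might infer that death-only events run against the kidney effect. With P = 0.09 this is not established, and more kidney events mechanically leave fewer deaths without one.
- A reader might infer that APRS could reach a good composite AUC by predicting death alone. Step 5 rules that out. It does not bound how much of the advantage over a comparator comes from death.

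The practical objection also stands in part: kidney-event counts are shown only for PMBB, so feasibility in ARIC (314 high-risk) and UK Biobank (204 high-risk) is unknown.

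**Conclusion.** The concern holds as a gap between aim and analysis. The stated aim is kidney outcomes, while every specified performance measure, and the protocol's NNT, rests on a composite in which 21.6% of derivation events and 25% of test-set events are deaths without a kidney event. No analysis is specified that would show how APRS performs for kidney events with death competing. That the score works mainly through death is neither shown nor excluded.

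On crude proportions the kidney-only NNT is 27.5% larger than the composite NNT. This assumes no drug effect on deaths without a kidney event. The documents do not say which outcome the 27% refers to, so the composite NNT cannot be called wrong outright, only unsupported for that component.

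The contradiction on censoring at death needs no assumption. Protocol 3.6 conflicts with its own component (3) and with SAP 6.3.1.

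**What to change.** - Keep the composite as primary. In Protocol 3.6/3.7 and SAP 6.3.1/7, add a key secondary kidney-only endpoint (≥40% eGFR decline, dialysis, transplantation) with death as a competing event.
- For the locked APRS and its comparators, report cause-specific Cox estimates and cumulative-incidence-based time-dependent AUC in PMBB, and in ARIC and UK Biobank where event counts allow. State how participants who die before the time point are classed. Base kidney-specific claims on this analysis.
- Beside the composite NNT, report one that applies the RRR to kidney-event cumulative incidence only, over the same RRR range, and state the assumption about deaths.
- Reword SAP 6.3.1 to say that the composite changes the outcome and does not estimate kidney risk under competing death.
- Reconcile Protocol 3.6 with SAP 6.3.1, so that death is coded one way for the composite and explicitly for the kidney-only endpoint.

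Cost: protocol and SAP wording, plus further analyses. In PMBB the events are already counted; in the external cohorts kidney-event counts must first be checked. Because the score is not refitted, its derivation is unaffected. The price is fewer events (120 against 153; 24 against 32 in the test set), hence wider intervals, and a less favourable NNT.
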